## Abstract

**Background:**

There has been longstanding interesting in cognitive training for older adults with cognitive impairment. In this study, we will investigate the effects of working memory training, and explore augmentation strategies that could possibly consolidate the effects in older adults with mild neurocognitive disorder. Transcranial direct current stimulation (tDCS) has been demonstrated to affect the neuronal excitability and reported to enhance memory performance. As tDCS may also modulate cognitive function through changes in neuroplastic response, it would be adopted as an augmentation strategy for working memory training in the present study.

**Methods/Design:**

This is a 4-week intervention double-blind randomized controlled trial (RCT) of tDCS. Chinese older adults (aged 60 to 90 years) with mild neurocognitive disorder due to Alzheimer’s disease (DSM-5 criteria) would be randomized into a 4-week intervention of either tDCS-working memory (DCS-WM), tDCS-control cognitive training (DCS-CC), and sham tDCS-working memory (WM-CD) groups. The primary outcome would be working memory test – the n-back task performance and the Chinese version of the Alzheimer’s Disease Assessment Scale – Cognitive Subscale (ADAS-Cog). Secondary outcomes would be test performance of specific cognitive domains and mood. Intention-to-treat analysis would be carried out. Changes of efficacy indicators with time and intervention would be tested with mixed effect models.

**Discussion:**

This study adopts the theory of neuroplasticity to evaluate the potential cognitive benefits of non-invasive electrical brain stimulation, working memory training and dual stimulation in older adults at risk of cognitive decline. It would also examine the tolerability, program adherence and adverse effects of this novel intervention. Information would be helpful for further research of dementia prevention studies.

**Trial registration:**

ChiCTR-TRC-14005036 Date of registration: 31 July 2014.

## Background

The World Alzheimer’s Report and World Health Organization (WHO) have highlighted dementia care as a public health priority [1, 2]. Despite increased understanding of putative pathological mechanisms, treatment options for dementia remains limited. Recent research has suggested that factors that influence the integrity and function of neuronal networks may help to resist the emergence of disabling clinical symptoms. Interventions that enhance neuroplastic response through stimulation may impact on cognitive impairments and possibly attenuate the trajectories of decline.

Cognitive impairment is the core syndrome of dementia. It also determines the loss of independent functioning. There has been long-standing interest as to whether cognitive training, programs with structured training of specific cognitive domains would help to improve cognition and function in people suffering from dementia [3–5]. In a recent study and a systematic review, it appeared that there was limited improvement in cognitive functions or behavior measures associated with cognitive training in people with dementia [6, 7]. However, other recent studies suggested a possibility of transferring cognitive benefits with working memory training paradigms. A working memory (WM) training task, the Adaptive n-back task, has recently been reported to offer improvements in cognitive domains other than working memory, including episodic memory and other measures of fluid intelligence [8, 9]. Improvements in performance were also found in older adults and were more marked in people with lower baseline performance [10]. This suggested that the n-back training has a potential to enhance cognitive reserve, whereas individual differences may be modulated by one’s capacity for neuroplastic response. However, replication studies published in 2013 were less promising. Transferrable cognitive benefits of n-back training beyond working memory tasks have not been demonstrated [11, 12]. Apart from differences in methodological designs, it is possible that cognitive training is able to effect overall improvement, but the transformation of underlying neuronal networks has been unstable. Before concluding that WM training is not beneficial for overall cognitive improvement, it is important to explore strategies that may augment and consolidate cognitive benefits.

Recent research suggests that non-invasive brain stimulation might enhance cognitive function [13]. Transcranial direct current stimulation (tDCS) is one promising option for exploration. The tDCS device generates a small electric current (usually 1 mA to 2 mA) to specific areas of the brain, and alters excitability of brain cells through polarity-dependent stimulation. Anodal stimulation of the brain areas generally enhances excitability, whereas cathodal stimulation reduces it. The manipulation of electrode positions and polarity would lead to different regional effects in brain areas. Anodal stimulation of the dorsal lateral prefrontal cortex (DLPFC) and temporal areas have been reported to enhance memory performance in healthy young and older-aged volunteers. In people suffering from Alzheimer’s disease (AD), recognition memory also appeared to improve after tDCS and effects persisted for a few weeks after intervention. A functional magnetic resonance neuroimaging study (fMRI study) reported that default mode network (DMN) activities in older adults showed a tendency for reversal to the pattern of the young adult volunteers after tDCS. This suggested possible physiological effects of enhanced neuroplastic response [14–19]. As for the safety and adverse event profiles, no major or serious adverse effects of tDCS had been reported in the past decade of research. The risk of inducing seizure was minimal.

Available evidence suggests that cognitive training is able to improve cognitive performance, at least in the domain being trained. Specifically designed working memory training may have an additional role of transferrable cognitive benefits. This suggested that our brain is responsive to mental stimulation with enhanced function. Electrical stimulation to the brain appeared to alter neuronal activities with corresponding changes in cognitive and other brain functions. It is possible that changes in neuroplasticity brought about by electrical stimulation would modulate the neural response to mental stimulation through cognitive training. The present study aims to examine the combined longer-term effects of tDCS working memory training, compared to single-modality intervention of either tDCS or WM, on cognition function.

## Methods/Design

A 4-week intervention (12-week observation) double-blind randomized controlled trial (RCT) of tDCS. Participants will be randomized into three groups:The working memory (Adaptive n-back) training-sham tDCS group (WM-CD).Participants would receive 20 minutes of sham tDCS, followed by 5 minutes of rest and 20 minutes of Adaptive n-back training.The tDCS-control cognitive training group (DCS-CC).Participants would receive 20 minutes of tDCS, followed by 5 minutes of rest and 20 minutes of controlled cognitive training with continuous performance tasks.The tDCS-working memory training (DCS-WM) group.Participants would receive 20 minutes of tDCS, followed by 5 minutes of rest and 20 minutes of Adaptive n-back training.

The intervention would be of 4 weeks duration, with 3 training sessions (45 minutes) per week. All groups would receive the same training schedule.

### Participants and recruitment

Participants would be recruited through existing research cohorts and local advertisements at older persons’ social centers in Hong Kong. Informed consent would be obtained from each eligible participant. Interested participants would first undergo a cognitive and clinical assessment for mild neurocognitive disorder due to AD (MND-AD) before recruitment for intervention. The cognitive assessment was derived from previous studies of the research team [20]. Potential participants would be assessed by psychiatrists of the research team for eligibility.

Inclusion criteria are as follows:Subjects from 60 to 90 years old;*Diagnostic and Statistical Manual of Mental Disorders, 5th edition* (DSM-5) diagnosis of MND-AD [18];

Exclusion criteria are set as:Previous diagnosis of other major neurocognitive disorders;Past history of bipolar affective disorder or psychosis;Physical frailty affecting attendance at training sessions;Already attending regular cognitive training;Taking a psychotropic or other medication known to affect cognition (e.g. benzodiazepines, anti-dementia medication, etc.);History of major neurological deficit including history of stroke, transient ischemic attack or traumatic brain injury;Significant communicative impairments

### Aims and hypotheses to be tested

The present proposal aims to address the above question with a paradigm having high potential for clinical practice. The proposed neuroenhancement intervention combined the dual approach of mental and electrical stimulation. We hypothesized thatAdaptive n-back task training (with sham tDCS) would be associated with improved test performance in both working memory and other cognitive domains.Stimulation to the right temporal cortex by tDCS (controlled cognitive training) would be associated with enhancement of test performance in memory and other cognitive domains. (Please refer to Intervention paradigms for details).The effects of improvement in global cognitive domains would be comparable in single- modality brain stimulation and Adaptive n-back training or tDCS.Combined tDCS and Adaptive n-back task training would be associated with more significant improvement in cognitive performance over single-modality brain stimulation by either Adaptive n-back task or tDCS.

### Randomization procedure

This will be a double-blind RCT of tDCS. Participants will be individually randomized into WM-CD, DCS-CC, or DCS-WM groups. Randomization with blocks of six would be adopted to ensure a balanced allocation of groups. The participants would be blind to the tDCS status. The assessors for clinical outcomes would be blinded to the randomization status. The staff who perform the intervention would not know the assessment results.

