## Trial status

Recruitment started in March 2015. Recruitment is ongoing.

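### A single published block size of six makes one allocation in five certain to anyone who knows every earlier arm; undisclosed varying sizes would remove most of these certainties, though little of the general guessability

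*Protocol article*

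**What the plan says.** The section Randomization procedure of the protocol article gives the allocation method: "Participants will be individually randomized into WM-CD, DCS-CC, or DCS-WM groups", and "Randomization with blocks of six would be adopted to ensure a balanced allocation of groups". No variation in size is mentioned. The section Trial status adds "Recruitment started in March 2015. Recruitment is ongoing".

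Blinding is described for three groups of people:

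- Participants: "The participants would be blind to the tDCS status".
- Outcome assessors: "The assessors for clinical outcomes would be blinded to the randomization status".
- Delivery staff: "The staff who perform the intervention would not know the assessment results". This keeps them from outcome data. It does not say that they are blind to arm or to active or sham stimulation.

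Eligibility is decided within the team: "Potential participants would be assessed by psychiatrists of the research team for eligibility" (Participants and recruitment). Some exclusions listed there, such as frailty that affects attendance and significant communication problems, call for judgement.

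According to Methods/Design, WM-CD and DCS-WM both train on the adaptive n-back task. Only DCS-CC uses the continuous performance task.

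**The concern.** In a fixed block the last places are determined by the earlier ones. Anyone who knows the block size and the arms already used can sometimes name the next arm before the next person is accepted. The block size is in print while allocations are still being made, and whoever runs a session sees which training task is given.

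If such knowledge reached the people who judge eligibility, acceptance could depend on the coming arm. The arms could then differ at entry. Blinded outcome assessment gives no protection against that, and adjustment in the analysis cannot be relied on to repair it. Knowing only the training type would already matter, because n-back performance is a primary outcome and the comparison of DCS-CC with the WM-CD reference group sets one training type against the other.

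**Working it through.** The article gives no figure for predictability, so there is none to reproduce.

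**Inputs**
- Block size 6 and three arms (Randomization procedure).
- Two places per arm in each block. This is an assumption, inferred from the stated aim of balance and the equal target per arm. No stratification is assumed.
- 64 per arm (Sample size estimation), so 3 × 64 = 192 participants, or 192/6 = 32 blocks.

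**Fixed sixes, all earlier arms known (including active or sham)**
- Possible blocks: 6!/(2!·2!·2!) = 90.
- The 6th allocation is always certain.
- The 5th is certain when the last two places belong to the same arm. That is 3 arms × 6 orders of the first four places = 18 blocks, and 18/90 = 0.2.
- Certain allocations per block: 1 + 0.2 = 1.2, and 1.2/6 = 20.0%. Over 192 participants this is 38.4.
- Best-guess success by position: 1/3, 2/5, 1/2, 8/15, 3/5, 1. The sum is 101/30 = 3.37, and 3.37/6 = 56.1%. Chance is 33.3%, so the excess is 22.8 points.

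**Fixed sixes, only training type known**

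Each block then looks like four n-back places and two control places.
- The next *arm* is certain only when control places alone remain. Each control place comes after all four n-back places with probability 1/5, so the expected number is 2 × 1/5 = 0.4 per block. 0.4/6 = 6.7%, or about 13 of 192.
- The next *training type* is also certain when only n-back places remain. Each n-back place comes after both control places with probability 1/3, which gives 4 × 1/3 = 1.333 per block. (0.4 + 1.333)/6 = 13/45 = 28.9%, or about 55 of 192.

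**Randomly varying sizes, all earlier arms known**

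Sizes are drawn with equal probability. The certain allocations come from simulated trials of 192 participants in which the observer knows the set of sizes but not which size is in use. The best-guess rate is exact for the rule of choosing an arm with the fewest allocations so far.

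| Sizes | Certain allocations | Best guess correct |
|---|---|---|
| 6 only | 20.0% | 56.1% |
| 3, 6 | 8.7% | 57.8% |
| 6, 9 | 5.3% | 54.4% |
| 6, 12 | 5.9% | 52.8% |
| 3, 6, 9 | 3.8% | 55.5% |
| 6, 9, 12 | 2.6% | 53.0% |

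A second simulation gave 2.3% certain for 6, 9 and 12, and 4.0% for 3, 6 and 9.

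With 6, 9 and 12, the certain allocations fall by (20.0 − 2.6)/20.0 = 87%. The excess of the best guess over chance falls only from 22.8 to 53.0 − 33.3 = 19.7 points, which is about 14%. The guessing rule does not use the block size, so hiding or varying the size hardly affects it.

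**The case against.** Fixed permuted blocks are an ordinary choice, and the randomization section contains no contradiction or miscalculation on this point. Three stronger readings are tempting, and the article supports none of them.

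- *That visible training type makes one allocation in five certain.* Two of the three arms share the n-back task, so training type cannot separate WM-CD from DCS-WM. The 20% also needs knowledge of active or sham stimulation. The article does not blind delivery staff to this, but it does not say that they know it either.
- *That varying the block size removes most of the selection risk.* It removes most certainties. Best-guess success hardly moves, and with sizes 3 and 6 it rises slightly.
- *That selection is happening, or that every contrast is biased.* Nothing says that the psychiatrists judging eligibility deliver sessions, see earlier allocations or know the order of entry. The article's silence is not evidence that they do.

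Two further limits stand. The count of 38 treats the whole trial as exposed, whereas publication can inform outsiders only about participants enrolled afterwards, and that number is not given. Who holds the list and when each allocation is released are details that an article may leave to the full protocol, so their absence is no fault here.

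The stated choice itself remains: one fixed size, in print during recruitment, for which a better and inexpensive alternative exists.

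**Conclusion.** The point holds in a limited form. With two places per arm in each block and no stratification, the published size makes 20% of allocations certain to an observer who knows every earlier arm in order. An observer who sees only training type is certain of the next arm in 6.7% and of the next training type in 28.9%. Undisclosed varying sizes would bring the 20% down to about 2 to 3% (6, 9 and 12) or about 4% (3, 6 and 9). The block-size sets are illustrative.

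This is a weakness in a stated method, not a demonstrated bias. Bias would arise only if those who enrol participants learn earlier allocations, and the article leaves that open.

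**What to change.** For the participants still to be recruited, generate a new list with block sizes that vary at random, for example 6, 9 and 12. Do not give the sizes in published text or to the staff who assess or treat. Because this leaves best-guess success at about 53%, also keep those who judge eligibility unaware of earlier allocations. If the full protocol already provides for that, a sentence saying so is enough.

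The cost is a regenerated list and a short amendment. The possible imbalance at the end is slightly larger. Within an unfinished block, two arms can differ by at most the number of places per arm, which is 6/3 = 2 for a block of six and 12/3 = 4 for a block of twelve. Against a target of 64 per arm this is small.

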### Definition of outcome measures (Appendix 1)

Primary outcomesWorking memory test – the n-back task performance at baseline, fourth, eighth and twelfth weeks would be recorded as a direct measure of improvement in task performance.Global Cognitive function would be measured by the Chinese version of the Alzheimer’s Disease Assessment Scale – Cognitive Subscale (ADAS-Cog). This is a standard global cognitive assessment for clinical intervention of AD. The scale score ranges from 0 to 70, with increasing scores indicating higher severity of global cognitive impairment [21].

Secondary outcomesMemory and language tests – logical memory, 10 minutes list learning delay recall, category verbal fluency and trail-making tests would also be evaluated to examine the effects of both tDCS and working memory training on other cognitive abilities [22].The Chinese Neuropsychiatric Inventory (NPI) [23] would be used to assess changes in neuropsychiatric symptoms across different twelve domains. In the current study, NPI would evaluate potential mood and behavioral change, especially mood and euphoria that may theoretically be affected by tDCS administration.A checklist of potential adverse effects associated with computer-based cognitive training and t-DCS administration would be generated from available literature reports. The checklist would be used to monitor tolerability and adverse events throughout intervention.

### Intervention paradigms

Working memory (Adaptive n-back) and Control cognitive training (Appendix 2)

n-back task is a continuous performance test proposed by Kirschner for measurement of working memory capacity. During the n-back task, subjects are usually presented with a sequence of stimuli, and required to indicate which stimulus matches the one from n steps earlier in the sequence. Adaptive n-back task refers to automatic adjustment of the level of difficulty of the task according to the accuracy of the performance. Participants with high degree of accuracy would be advanced to another level of difficulty, whereas a suboptimal performance would be adjusted to an easier practice level [24, 25]. The Adaptive n-back visual training paradigm (WM) is programed using the E-Prime. The adaptive training offers a feedback mechanism and has a higher demand for attention throughout the training session. As the participants are older adults with little previous computer experience and may be more limited in working memory capacity, visual stimuli would be offered for training at the initial five levels. The dual task with auditory-visual stimuli would be offered after the participant has passed the 6-back training. It is considered that this approach would ensure higher motivation for long-term practice.

The Control cognitive training (CC) would be a continuous performance test paradigm. This is considered as an active control as the paradigm demands sustained attention similar to the n-back task. However, it does not offer training of the working memory component embedded in the n-back task.2.Transcranial direct current stimulation (tDCS)

### Statistical analyses

Multilevel generalized linear modeling would be employed to account for the correlations from within subjects and different time points of measurement. Baseline cognitive characteristics between tDCS-working memory training (DCS-WM), tDCS-control cognitive training group (DCS-CC) and working memory training–-ham tDCS (WM-CD) groups would be evaluated. Changes of cognitive function and behavioral symptoms from baseline to each follow-up point and intervention differences would be tested with occasions (time points) at level 1 and subjects at level 2. Global cognitive function between DCS-WM, DCS-CC would be made with WM-CD (reference group). Covariates including baseline differences would be entered in the regression model. Secondary analyses of specific cognitive function would be performed to compute for group differences in outcome. Incidence of adverse events and characteristics of program adherence would be recorded. Statistical significance will be set at *p* < 0.05. Bonferroni corrections would be adopted for adjustment of multiple comparisons. Computations would be performed using SPSS (SPSS Inc., Chicago, IL, USA) for windows version 20.0 and Stata (StataCorp, College Station, TX, USA).

### Ethical consideration

A psychogeriatrician who is familiar with mental capacity assessment would assess mental capacity for participation in this research. Participants would be recruited if they are considered mentally fit to sign consent. First degree relatives of participants will also be informed before intervention. Ethics approval from The Joint Chinese University of Hong Kong – New Territories East Cluster Clinical Research Ethics Committee has been obtained, and the protocol registered with the Center for Clinical Research and Biostatistics, Clinical Trials Registry of the Chinese University of Hong Kong and linked to the Chinese Clinical Trials Registry (ChiCTR), World Health Organization – International Clinical Trials Registry Platform (WHO-ICTRP) China Primary Registry (ChiCTR-TRC-14005036). The study will comply with the Declaration of Helsinki and the Good Clinical Practice guidelines of the International Conference on Harmonization of technical requirements for registration of pharmaceuticals for human use (ICH-GCP). The results will be reported according to Consolidated Standards of Reporting Trials (CONSORT) Guidelines for non-pharmacological interventions.

## Discussion

The present study aims to examine the cognitive effects of working memory training in older adults with MND-AD, and to evaluate whether the effects would be transferrable to other cognitive domains. The findings, if positive, would provide a basis for enhancement of cognitive reserve through brain stimulation. Second, we would also evaluate the cognitive effects of tDCS. The information would help to address the impact of electrical stimulation on brain function, which would bring insights into therapeutic potential of other psychiatric disorders associated with cognitive dysfunction. More importantly, we hope to examine if adjuvant electrical stimulation would consolidate the brain response through manipulation of neuroplasticity. This would provide directions for research in the neurophysiological basis of synergistic brain stimulation of different modalities.

From a clinical perspective, the current proposal would serve as a Phase 2 non- pharmacological intervention. It would examine the potential efficacy of cognitive training, electrical brain stimulation, and dual mental and electrical brain stimulation. The proposed study would also examine the tolerability, program adherence and adverse effects of this intervention in older adults. As stipulated by a recent report by the Alzheimer’s Australia, an intervention that delays the onset by 2 years will reduce the prevalence of dementia by 13 % in 3 decades [27]. If the findings suggest potential positive benefits, and with low risks, the proposed intervention would provide a solid basis for further evaluation by further Phase 3 clinical trials with implementation in clinical settings for dementia prevention.

